#### Power analysis for primary outcomes

All power calculations were conducted in Power Analysis and Sample Size (PASS) 2023. Power was calculated at alpha=0.05 with 200 patients at five timepoints. For all power estimates, we assumed an 8% mortality rate between primary timepoints; therefore, 28% of patients will be deceased by the 12 month time point (American Cancer Society, 2019). Power calculations were conducted with missing timepoints rather than on imputed data since we plan to compare imputed to non-imputed models. We further assumed an exchangeable correlation structure with a moderately strong intraclass correlation (r = 0.6).

Many estimates were obtained through the pilot analysis. We conducted an observational, pre-test/post-test pilot study in which we recruited 150 financially burdened cancer patients and provided them with a one-time grant of $1,000. We measured primary and secondary outcomes of interest prior to the intervention delivery and two months after to examine changes over time. We expect that the full trial, which will provide participants with 12 times the amount of cash that was provided in pilot, will yield higher treatment effects. We believe the estimates from the pilot are conservative estimates for the full trial, and any estimates not obtained from the pilot were overly conservative to ensure full power.

##### Financial toxicity

The pilot analysis saw a mean COST difference of 2.4 units (Treatment = 12.9, control = 10.5) and an overall standard deviation of 7.1 units. We expect the covariates we control for in the linear mixed model to have a moderate to moderately strong correlation (between 0.5 and 0.8). Although we expect to observe a larger mean COST difference in the full trial, we calculate the power of our full trial to be between 0.867 and 0.993.

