##### Treatment nonadherence

The pilot analysis saw a mean 30-day nonadherence rate of 11.5% for the control group and a mean nonadherence of 14.7% for the treatment group. We did not expect to observe an increase in nonadherence from pre to post intervention and do not have sound evidence to explain it. However, we can infer that because we only provided the pilot group with a one-time payment of $1,000, that this amount was insufficient to produce changes in 30-day nonadherence. Although we do not have sufficient evidence to corroborate nonadherence rates for our treatment group, we found the nonadherence rate for our control group to be somewhat lower than previous research on nonadherence in financially burdened cancer patients (Zullig et al., 2013; Costas-Muniz et al., 2016; Lee and Khan, 2016; Lee and Salloum, 2016; Nipp et al., 2016; Knight et al., 2018; Zhao et al., 2019). Two past studies that focused on reducing nonadherence to chemotherapy using a behavioral intervention to improve quality of life found significantly lower nonadherence to chemotherapy rates in the intervention group (19%) than in the control group (62.5%) (Cheville et al., 2015). We expect the covariates we control for in the GEE model to have a moderate to moderately strong correlation (between 0.5 and 0.8). Thus, we calculate the power to detect any difference between the treatment and control group to be between 0.065 and 0.095. If the nonadherence rate for our the trial treatment group is similar to the pilot, we will need to observe a nonadherence for the control group to be at least 32% which is possible given the nonadherence rates observed in past studies.

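### The COST power enters an uncontrolled pre/post change from a single-group pilot as the difference between randomized arms, so the stated power and the claim that it is conservative are unsupported

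*Protocol article*

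**What the plan says.** The section Power analysis for primary outcomes describes the source of the planning values: "We conducted an observational, pre-test/post-test pilot study in which we recruited 150 financially burdened cancer patients and provided them with a one-time grant of $1,000". Outcomes were taken "prior to the intervention delivery and two months after to examine changes over time". No untreated group is mentioned.

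The Financial toxicity paragraph of the power section then gives a treatment value and a control value: "The pilot analysis saw a mean COST difference of 2.4 units (Treatment = 12.9, control = 10.5"), with "an overall standard deviation of 7.1 units". From these it states power of 0.867 to 0.993, for covariate correlations of 0.5 to 0.8. The Quality of life paragraph uses the same labels for the SF-36 (39.8 and 36.4, difference 3.4, SD 29.4; power 0.1831 to 0.3294). The Treatment nonadherence paragraph does so again: "mean 30-day nonadherence rate of 11.5% for the control group and a mean nonadherence of 14.7% for the treatment group".

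The nonadherence paragraph goes on to say what those labels stand for: "We did not expect to observe an increase in nonadherence from pre to post intervention".

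On the standing of these values the protocol says: "We believe the estimates from the pilot are conservative estimates for the full trial". The reason given is that the trial pays twelve times the pilot amount.

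**The concern.** The trial compares cash with concurrent treatment as usual in randomized arms. A before/after change in patients who were all paid is a different quantity. It contains whatever would have happened over two months without the grant, including time trend and, in patients recruited because they were financially burdened, regression to the mean. Such change occurs in both arms of a randomized trial and cancels from the comparison, but it stays in the pilot's 2.4 units.

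COST is the only primary outcome for which the protocol states adequate power. SF-36 power is at most 0.33 at the pilot difference, and nonadherence power is 0.065 to 0.095. If the COST planning difference has no basis as a between-arm effect, the one reassuring power figure has none either, and the treatment/control labels hide this from the reader.

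**Working it through.** **1. What the labels mean.** The pilot description gives one group, all paid, measured twice. The nonadherence paragraph calls the move from 11.5% (labelled control) to 14.7% (labelled treatment) a pre-to-post increase. So control is the pre-grant value and treatment the post-grant value. The protocol does not say this outright for COST or the SF-36. It follows from the design and from the nonadherence wording.

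**2. Reproducing the stated power.** Inputs from the power section: alpha 0.05 (two-sided assumed, as the side is not stated), 200 patients, five timepoints, 8% loss per interval, exchangeable correlation 0.6, covariate correlation r = 0.5 to 0.8, COST difference 2.4 and SD 7.1. The split of the 200 is not stated, so 1:1 and 1:1.5 were both tried.

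- Patients by timepoint: 200, 184, 169.3, 155.7, 143.3; mean 170.5.
- Variance factor for a mean of five visits: (1 + 4 × 0.6)/5 = 0.68.
- Adjusted SD = 7.1 × √(0.68 × (1 − r²)) = 5.07 (r = 0.5) and 3.51 (r = 0.8).
- SE at 1:1 = adjusted SD × √(4/170.5) = 0.777 and 0.538.
- z = 2.4/SE = 3.09 and 4.46. Power = Φ(z − 1.96) = 0.871 and 0.994.

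The protocol states 0.867 and 0.993. A 1:1.5 split gives 0.857 and 0.992. The same formula for the SF-36 at 1:1 (3.4, SD 29.4) gives 0.183 and 0.332, against 0.1831 and 0.3294. The calculation is therefore a two-group, between-arm one, and the pilot's pre/post change is its difference.

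**3. Power over assumed between-arm differences.** The protocol gives no between-arm estimate, so these differences are assumptions. All other inputs are as in step 2, with a 1:1 split.

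| Assumed COST difference | Power, r = 0.5 | Power, r = 0.8 |
|---|---|---|
| 1.2 | 0.34 | 0.61 |
| 1.8 | 0.64 | 0.92 |
| 2.4 | 0.87 | 0.99 |
| 3.0 | 0.97 | above 0.99 |

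**4. Difference detectable with 80% power** = (1.96 + 0.84) × SE.

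- COST: 2.80 × 0.777 = 2.2 (r = 0.5) and 2.80 × 0.538 = 1.5 (r = 0.8).
- SF-36: SE = 29.4/7.1 × the COST SE = 3.22 and 2.23, so 9.0 and 6.2. Using the SE implied by the protocol's stated COST power instead (2.4/3.07 = 0.781 and 2.4/4.42 = 0.543) gives 9.1 and 6.3. The two routes agree to within 0.1.
- The protocol's own SF-36 figure of 6.5 for full power: 6.5/3.22 = 2.02, power 0.52 at r = 0.5; 6.5/2.23 = 2.92, power 0.83 at r = 0.8. It gives about 80% power only near the favourable end of the stated covariate range.

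**The case against.** The strongest reply is that the formula does address the two-arm contrast and that the stated power is correct whenever the true between-arm difference is at least 2.4, whatever produced the pilot change. The protocol gives a reason to expect this: twelve payments instead of one. If only half the pilot change was due to cash but the longer intervention doubled that effect, the difference would again be 2.4. Untreated patients may also worsen. The research hypothesis speaks of preventing financial toxicity, and in that case a pre/post gain would understate the between-arm effect. This stands. A reader might infer that the power is right only if the whole pilot change was caused by cash, or that the trial is shown to be underpowered for COST. The documents support neither.

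What the reply does not do is supply a basis for 2.4. The twelve-fold argument is about the amount of cash. It says nothing about change that would occur without cash, so it cannot make the pilot value conservative.

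A reader might also infer that the nonadherence power is power to detect harm, since the pilot rate rose. The protocol speaks of power to detect any difference, reports the unexpected direction openly and discloses the very low figure. The COST-type formula applied to 11.5% and 14.7% gives about 0.14 to 0.24, not 0.065 to 0.095, so how those rates entered the calculation cannot be confirmed. The narrower statement holds: a change in the unfavourable direction cannot be a conservative estimate of benefit.

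Finally, the protocol says that funding set the sample size and that the power work was done to find detectable effects. It already gives 6.5 for the SF-36 and a needed control rate of 32% for nonadherence. So part of the remedy is present, but a detectable difference for COST is not.

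**Conclusion.** The point holds as a fault in the source and labelling of the planning difference, not in the power arithmetic. The COST power of 0.867 to 0.993 rests on a single-group pre/post change entered as a between-arm effect. That change does not estimate cash versus concurrent usual care, so both the power and its description as conservative are unsupported. The SF-36 and nonadherence pilot values have the same defect.

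The size and direction of the error cannot be fixed from the documents. Halving the assumed difference to 1.2 units lowers COST power to 0.34 to 0.61, and raising it to 3.0 gives 0.97 or more. These figures assume a two-sided 5% test, a 1:1 split and the protocol's loss, correlation and SD. The conclusion also rests on reading control as pre-grant for COST. If a separate untreated pilot group did exist, the pilot description and the nonadherence paragraph would need correcting instead.

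**What to change.** - In the Financial toxicity, Quality of life and Treatment nonadherence paragraphs of the power section, relabel the pilot values as pre-grant and post-grant.
- Remove the description of the pilot estimates as conservative. The expectation of a larger effect from twelve payments can stay if it is worded as an expectation.
- State planning as the between-arm difference detectable with 80% power: COST about 2.2 units (r = 0.5) to 1.5 (r = 0.8); SF-36 about 9.1 to 6.3. Note beside the existing 6.5 that it gives about 80% power only near r = 0.8, and about 0.52 at r = 0.5.
- Show COST power for assumed differences on both sides of 2.4, as in the table above, and state the sidedness and allocation split used.

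The cost is restated figures and a few sentences. Sample size is fixed by funding, and randomization, outcomes and analysis are untouched.

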##### Quality of life

The pilot analysis saw a mean SF-36 aggregate score difference of 3.4 units (Treatment = 39.8, control = 36.4) and an overall standard deviation of 29.4 units. We expect the covariates we control for in the linear mixed model to have a moderate to moderately strong correlation (between 0.5 and 0.8). Although we expect to observe a larger mean SF-36 aggregate score difference in the full trial, we calculate the power of our full trial to be between 0.1831 and 0.3294. In order to be fully powered, we will need to observe a mean SF-36 aggregate score difference of at least 6.5 assuming similar standard deviations. Although this is 2.9 units larger than observed in the pilot, we expect to see a larger difference between the treatment and control groups because of the compounding effect of monthly UCT relative to treatment as usual.

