#### Trial design

The GIFT Trial is designed as a randomized, controlled, unblinded, multicenter superiority trial with two parallel groups and a combined primary endpoint of financial toxicity, quality of life, and treatment adherence. Randomization will be performed as block randomization with a 1:1.5 allocation stratified by age and treatment center.

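### The single SF-36 difference given for full power (6.5) holds only near the most favourable covariate correlation; at the other end of the protocol's range about 9.1 is needed, and the stated excess over the pilot (2.9) is mis-subtracted

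*Protocol article*

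**What the plan says.** The protocol article, under *Power analysis for primary outcomes*, sets the common assumptions: "Power was calculated at alpha=0.05 with 200 patients at five timepoints", deaths of 8% between timepoints, and an exchangeable within-patient correlation of 0.6.

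Under *Quality of life* it gives a pilot difference of 3.4 (39.8 versus 36.4) and a standard deviation of 29.4. It expects the covariates "to have a moderate to moderately strong correlation (between 0.5 and 0.8") and reports power as a range, 0.1831 to 0.3294. To reach full power, it continues, "we will need to observe a mean SF-36 aggregate score difference of at least 6.5 assuming similar standard deviations". The next sentence compares this with the pilot: "Although this is 2.9 units larger than observed in the pilot".

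The article does not say which covariate correlation the 6.5 assumes or what level of power counts as full.

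**The concern.** Two things do not fit.

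1. Power is reported as a range because the covariate correlation is uncertain. The detectable difference depends on that correlation just as strongly, yet it is given as one number whose only stated condition is the standard deviation. A reader will take 6.5 as sufficient over the whole 0.5 to 0.8 range.
2. The pilot difference (3.4), the required difference (6.5) and the stated excess (2.9) cannot all be right.

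Quality of life is one of three primary outcomes. The article concedes low power at the pilot effect and relies on this threshold, together with the larger total payment, to argue that adequate power is attainable. If 6.5 is only the best case, a non-significant SF-36 result could be read as evidence against an effect of that size when the trial had roughly an even chance of detecting it.

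**Working it through.** **Inputs (protocol article).** Alpha 0.05, 200 patients, five timepoints, within-patient correlation 0.6, 8% loss between timepoints (*Power analysis for primary outcomes*); allocation 1:1.5, so 80:120 of 200 (*Trial design*); difference 3.4, SD 29.4, covariate correlation r from 0.5 to 0.8, powers 0.1831 and 0.3294 (*Quality of life*). Assumptions added here: a two-sided test, and full power meaning 80%, with 90% shown alongside.

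**Step 1. Reproduce the stated powers.** For the treatment main effect in a repeated-measures model,

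SE = SD × √[ (1 − r²)/I × (1/80 + 1/120) ],

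where I is the information per patient: the sum, over the number m of completed visits, of P(m) × m/(1 + (m − 1) × 0.6). With 8% loss at each of the five timepoints, the first included, I = 1.294.

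- r = 0.5: SE = 29.4 × √(0.75/1.294 × 0.02083) = 3.23; power at 3.4 = 0.1834 (stated 0.1831).
- r = 0.8: SE = 29.4 × √(0.36/1.294 × 0.02083) = 2.24; power at 3.4 = 0.3299 (stated 0.3294).

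The same set-up gives 0.868 and 0.993 for COST, against the stated 0.867 and 0.993. The method behind the figures is therefore identified.

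**Step 2. Back-solve from the printed powers alone.** This needs no assumption about allocation, loss or within-patient correlation. With λ = 3.4/SE and two-sided power Φ(λ − 1.960) + Φ(−λ − 1.960):

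- Power 0.1831 gives λ = 1.051, so SE = 3.4/1.051 = 3.23.
- Power 0.3294 gives λ = 1.518, so SE = 3.4/1.518 = 2.24.

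The ratio of the two SEs is 1.443, which equals √(0.75/0.36). The two powers are thus the two ends of the correlation range.

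**Step 3. Required difference and power at 6.5.** Required difference = (1.960 + 0.842) × SE for 80% power and (1.960 + 1.282) × SE for 90%.

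| Covariate correlation | Needed for 80% power | Power at 6.5 |
|---|---|---|
| 0.5 | 9.06 | 0.52 |
| 0.6 | 8.37 | 0.59 |
| 0.7 | 7.47 | 0.68 |
| 0.8 | 6.28 | 0.83 |

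For 90% power the ends are about 10.5 (r = 0.5) and 7.3 (r = 0.8).

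**Step 4. The subtraction.** 6.5 − 3.4 = 3.1, not 2.9. Conversely 3.4 + 2.9 = 6.3, which is the rounded 80% value at r = 0.8. Either 6.5 or 2.9 may be the mistaken figure.

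**Step 5. Sensitivity to the loss assumption.** The article's text says "we assumed an 8% mortality rate between primary timepoints; therefore, 28% of patients will be deceased by the 12 month time point". Its printed powers are matched only if loss also applies at the first timepoint, which leaves 0.92⁵ = 0.659 at the fifth, or 34% lost. With loss starting after baseline (0.92⁴ = 0.716, 28% lost), I = 1.407. The required differences become 8.7 and 6.0, and power at 6.5 becomes 0.56 and 0.86. The pattern is the same.

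**The case against.** The strongest defence is that the sentence sets a lower bound. Read that way it is not false: below about 6.3 units no correlation in the range gives 80% power, and 6.5 does give it at 0.8. That reading is available, but the article does not label the figure as a best case. It states what full power requires, directly after a power range, and names only the standard deviation as a condition. The same power section describes its non-pilot inputs as conservative, which an unlabelled best case is not.

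Three further points carry some weight.

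- The 80% target is this review's assumption. That stands and must be said, but a 90% target makes 6.5 insufficient at every correlation in the range.
- The replacement figures inherit the standard errors behind the printed powers, which do not match the stated 28% mortality. That also stands, but correcting it only moves 6.3 and 9.1 to 6.0 and 8.7.
- The harm is limited. The article openly reports power of 0.18 to 0.33 at the pilot effect, and *Sample size* says funding set the number of participants, so no design choice rests on 6.5. This is fair: the consequence lies in interpretation, not in the conduct of the trial.

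No defence was found for the subtraction.

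**Conclusion.** The concern holds. From the article's own powers, 80% power for the SF-36 aggregate score needs about 6.3 units at covariate correlation 0.8 and 9.1 at 0.5, which is 1.8 to 2.7 times the pilot difference (6.28/3.4 and 9.06/3.4). The single figure of 6.5 understates the requirement by about 2.6 units at the lower correlation, where power at 6.5 is 0.52. Even at 0.7 it is 0.68. The stated excess of 2.9 contradicts 6.5 − 3.4 = 3.1.

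The exact thresholds rest on a two-sided 5% test and an 80% target. The dependence on the correlation and the subtraction error do not. This should be corrected, as a matter of reporting.

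**What to change.** Replace the single threshold with a range that names its target. For example: 80% power requires a difference of about 6.3 units at covariate correlation 0.8 and about 9.1 at 0.5, that is 2.9 to 5.7 units above the pilot difference of 3.4. If the authors meant another target, give its range instead (for 90%, about 7.3 to 10.5).

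If 6.5 is kept, state the correlation and power it belongs to and correct the excess to 3.1. The authors should check their power output to see whether 6.5 or 2.9 was mistyped. If they rerun the calculation with loss starting after baseline, so that it matches 28% by month 12, the 80% figures become about 6.0 and 8.7, and the printed powers must be updated with them.

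The cost is a few words and a less favourable statement for this outcome. Sample size, endpoints and analysis are unaffected.

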##### Treatment nonadherence

The pilot analysis saw a mean 30-day nonadherence rate of 11.5% for the control group and a mean nonadherence of 14.7% for the treatment group. We did not expect to observe an increase in nonadherence from pre to post intervention and do not have sound evidence to explain it. However, we can infer that because we only provided the pilot group with a one-time payment of $1,000, that this amount was insufficient to produce changes in 30-day nonadherence. Although we do not have sufficient evidence to corroborate nonadherence rates for our treatment group, we found the nonadherence rate for our control group to be somewhat lower than previous research on nonadherence in financially burdened cancer patients (Zullig et al., 2013; Costas-Muniz et al., 2016; Lee and Khan, 2016; Lee and Salloum, 2016; Nipp et al., 2016; Knight et al., 2018; Zhao et al., 2019). Two past studies that focused on reducing nonadherence to chemotherapy using a behavioral intervention to improve quality of life found significantly lower nonadherence to chemotherapy rates in the intervention group (19%) than in the control group (62.5%) (Cheville et al., 2015). We expect the covariates we control for in the GEE model to have a moderate to moderately strong correlation (between 0.5 and 0.8). Thus, we calculate the power to detect any difference between the treatment and control group to be between 0.065 and 0.095. If the nonadherence rate for our the trial treatment group is similar to the pilot, we will need to observe a nonadherence for the control group to be at least 32% which is possible given the nonadherence rates observed in past studies.

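### The stated nonadherence power (0.065 to 0.095) lies below the roughly 0.11 that the plan's inputs give without covariates, so the shared covariate correlation appears to lower power here while raising it for COST and SF-36

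*Protocol article*

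**What the plan says.** The opening of Power analysis for primary outcomes sets one basis for all three outcomes: "Power was calculated at alpha=0.05 with 200 patients at five timepoints". It adds "we assumed an 8% mortality rate between primary timepoints; therefore, 28% of patients will be deceased by the 12 month time point", an exchangeable within-patient correlation of 0.6, and "Power calculations were conducted with missing timepoints rather than on imputed data". The three outcome subsections then give the same covariate correlation range, 0.5 to 0.8.

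- **Financial toxicity (COST):** difference 2.4, SD 7.1; "we calculate the power of our full trial to be between 0.867 and 0.993".
- **Quality of life (SF-36):** difference 3.4, SD 29.4; power 0.1831 to 0.3294.
- **Treatment nonadherence:** pilot rates 11.5% (control) and 14.7% (treatment); "we calculate the power to detect any difference between the treatment and control group to be between 0.065 and 0.095". If the treatment arm stays near its pilot rate, "we will need to observe a nonadherence for the control group to be at least 32" per cent, which the text calls possible in view of past studies.

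None of the subsections says how the correlation enters the calculation. Sidedness and the split of the 200 patients between arms are not given, nor is the target power behind the 32%. Trial design states: "Randomization will be performed as block randomization with a 1:1.5 allocation stratified by age and treatment center".

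**The concern.** With common inputs and a common correlation range, covariate adjustment should act in the same direction for every outcome, or at worst give no benefit for a binary one. It should not help two outcomes and harm the third. A nonadherence range that sits wholly below the no-covariate value suggests that a different and unsuitable adjustment was used.

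Nonadherence is one of three primary outcomes. The article also uses the 32% control rate to argue that adequate power is attainable. A wrong power, or a threshold with no stated basis, misdescribes what the trial can detect on this outcome.

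**Working it through.** **Inputs.** From the article: alpha 0.05, N = 200, five timepoints, ICC 0.6, 8% mortality per interval, covariate r of 0.5 or 0.8, and the effects and SDs above. Assumed because not stated: two-sided test (z = 1.96), 100:100 split (80:120 also tried), and 80% target power for the control rate.

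**Repeated-measures factor.** Mean retention over five visits is (1 + 0.92 + 0.8464 + 0.7787 + 0.7164)/5 = 0.852. Factor = [1 + 4(0.6)]/5 / 0.852 = 0.798. For 100:100, v = (2/100)(0.798) = 0.01596 and √v = 0.1263.

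**Power.** λ = effect/(SD·√v) and power = Φ(λ - 1.96), counting one rejection tail. Multiplying variance by (1 - R²) divides λ by √0.75 at r = 0.5 and by 0.6 at r = 0.8. Dividing variance by (1 - R²) multiplies λ by the same quantities.

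**Step 1: COST and SF-36.**

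| Outcome | λ, no covariates | No covariates | Variance × (1 - R²), r = 0.5 to 0.8 | Variance ÷ (1 - R²), r = 0.5 to 0.8 | Stated |
|---|---|---|---|---|---|
| COST | 2.4/(7.1 × 0.1263) = 2.68 | 0.763 | 0.871 to 0.994 | 0.640 to 0.362 | 0.867 to 0.993 |
| SF-36 | 3.4/(29.4 × 0.1263) = 0.915 | 0.148 | 0.183 to 0.332 | 0.122 to 0.079 | 0.1831 to 0.3294 |

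Of these forms, only variance reduction fits. As a check free of v, the ratio of the two λ values implied by the stated SF-36 powers (both tails) is 1.443, and √(0.75/0.36) = 1.443.

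**Step 2: nonadherence, same factor.** λ = 0.032/√[0.798(0.147 × 0.853 + 0.115 × 0.885)/100] = 0.032/0.0426 = 0.752.

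| Covariate treatment | r = 0.5 | r = 0.8 |
|---|---|---|
| None | 0.113 | 0.113 |
| Variance × (1 - R²) | 0.137 | 0.240 |
| Variance ÷ (1 - R²) | 0.095 | 0.066 |
| Stated range | 0.095 (upper end) | 0.065 (lower end) |

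On the log-odds scale the divided form gives 0.0949 and 0.0655. With 80:120 it gives 0.092-0.094 and 0.064-0.065, and the no-covariate value is 0.109-0.112. Counting both tails, the no-covariate value is 0.116-0.117 (100:100), and the divided form gives 0.099-0.100 and 0.073-0.074.

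**Step 3: control rate needed against 14.7% in the treatment arm** (100:100; risk-difference to log-odds scale).

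| Basis | Control rate |
|---|---|
| No covariate effect, 80% power | 29.1% to 29.6% |
| Variance × (1 - R²), 80%, r = 0.5 | 27.0% to 27.4% |
| Variance × (1 - R²), 80%, r = 0.8 | 23.0% to 23.1% |
| Variance ÷ (1 - R²), 80%, r = 0.5 | 31.6% to 32.4% |
| Variance ÷ (1 - R²), 80%, r = 0.8 | 39.9% to 42.3% |
| No covariate effect, 90% power | 31.6% to 32.5% |

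With 80:120 on the log-odds scale, the first two rows become 30.5% and 28.0%.

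**The case against.** **The mechanism is not documented.** This stands: the variance penalty is an inference. The close match counts one rejection tail, and with both tails it is looser. The upper bound has another possible source: a plain two-proportion test on 170 patients (200 times mean retention) gives about 0.095 with both tails counted and no covariate term. That route does not explain the lower bound of 0.065, and it leaves out the covariate effect that the article says it assumes. The observation that the stated range falls below the no-covariate value does not depend on the mechanism.

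**A reader might infer that the 32% comes from the penalised calculation, holds only at r = 0.5, and is therefore wrong.** The documents do not support that. The target power is never given. About 32% also results at 90% power with no covariate effect, and a plain 80% power test on 200 patients at one timepoint gives 31.3% to 31.8%. What can be said is that the 32% has no stated basis.

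**A single replacement figure would be too definite.** This stands. Setting the treatment-covariate R² to 0 gives no covariate gain, which differs from the convention behind COST and SF-36. For a logit GEE the (1 - R²) gain is only approximate.

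**The impact is small.** Largely true. The article already reports power below 10%, the sample size was set by funding, and the stated figures err on the pessimistic side. That limits the consequence, but it does not make the stated power right.

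**Conclusion.** The point holds as an inconsistency in the power calculation. From the article's own inputs, COST and SF-36 reproduce with covariates raising power, while the nonadherence range lies wholly below the no-covariate value of about 0.11. It matches variance divided by (1 - R²). That penalty belongs to covariates correlated with treatment, which randomisation rules out in expectation.

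The correction moves power from 0.065-0.095 to about 0.11-0.12 with no covariate gain, or to about 0.13-0.14 (r = 0.5) up to 0.23-0.24 (r = 0.8) with the gain used elsewhere. The 32% cannot be called wrong, only unanchored: at 80% power the rate is about 29-30% with no gain, and about 27-28% (r = 0.5) or 23% (r = 0.8) with it.

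This rests on a two-sided 0.05 test, a 100:100 or 80:120 split, 80% target power and a normal approximation. A reader might infer that the corrected calculation rescues this outcome. It does not: at the pilot rates, which also run in the unfavourable direction, power stays far below 80% on every basis.

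**What to change.** - Rerun the nonadherence power with the treatment-covariate R² set to 0, and report about 0.11 to 0.12 as the conservative value with no covariate gain.
- If the COST and SF-36 convention is preferred, report about 0.13-0.14 (r = 0.5) to 0.23-0.24 (r = 0.8), and note that this gain is approximate for a logit GEE.
- Recompute the required control rate on the chosen basis, and state its target power and correlation.
- Add one sentence saying how the covariate correlation enters each of the three calculations, with the sidedness and the arm split used.

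The cost is one rerun, two changed figures and a sentence of explanation. Trial conduct and sample size are unaffected.
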